PCI receiving intersectoral care management during the transition from hospital to their homes and into primary care will have better patient-oriented health outcomes than PCI receiving care as usual (CAU) at 3 and 12 months after discharge.PCI receiving intersectoral care management during the transition from hospital to home will have a lower frequency of unscheduled readmissions to hospital than PCI receiving CAU.PCI receiving intersectoral care management during the transition from hospital to home are less likely to be institutionalized 12 months after discharge from hospital than PCI receiving CAU.

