### Outcomes

The primary objective of the study is to evaluate the efficacy of intersectoral care management for elderly PCI admitted to hospital. Primary outcomes are ADL (which are a proxy for functionality after discharge), unscheduled readmissions, and premature institutionalization.

They are measured as follows:
*Activities of daily living* will be assessed using the Bayer Activities of Daily Living Scale (B-ADL) [31], which consists of 25 items on everyday problems and challenges. The questionnaire targets community-dwelling patients who suffer mild cognitive impairment or mild-to-moderate dementia. It assesses the patient’s competence with general ADL and specific tasks in everyday life in the following domains: medication, hygiene, reading, conversation, telephoning, shopping, food preparation, handling money and financial affairs, using household appliances, transportation, leisure activities, everyday tasks that require unimpaired short- or long-term memory, and orientation in familiar and unfamiliar surroundings. The B-ADL also assesses nonspecific tasks requiring cognitive functions for the management of everyday life. These include remembering where to continue with an ongoing task after an interruption, doing two things at the same time, coping with unfamiliar or new situations that require the processing of new information, as well as the safety aspects of ADL and difficulties performing a task when under pressure.To assess *readmissions to hospital*, each participant will be asked how many times they have been hospitalized (unplanned and planned) within the last 12 months. This is one item in the Questionnaire on the Use of Medical and Non-Medical Services in Old Age (FIMA) [32], which is administered to assess utilization of health services. FIMA examines socioeconomic variables and other medical factors to determine health-related costs.*Institutionalization* will be assessed during the study, since the participants’ living situation will be checked at each assessment.

The secondary outcomes of this trial are not explicitly targeted by the intervention but were chosen as important moderating or mediating factors. Among those, we consider the following: (a) frailty, (b) delirium, (c) quality of life, (d) cognitive status, (e) neuropsychiatric symptoms, (f) utilization of health services, and (g) informal caregiver burden. We assume that (a), (b), and (f) are moderating factors and that (c), (d), (e), and (g) are mediating factors.

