Immediately following randomization, standardized and systematic feedback based on clinically relevant parameters ascertained in the baseline assessment will be issued to the treating hospital staff (hospital information letter) in both groups. The letter includes assessment data. For the intervention group, it additionally includes recommendations for treatment and care for the discharge plan and for the preparation of ambulatory services, medication, social integration, and medical treatment after discharge. In both groups, the participant’s medical status at the time of discharge will be documented in their record. Patients in the intervention group will be contacted immediately after discharge, if possible in person, to continue the delivery of the intervention as outlined above. Otherwise, telephone contact is initiated with the intention to plan a timely in-person visit or visits by the specifically trained study nurses.

Follow-up assessments of all outcome measures for both groups will be conducted 3 months and 12 months after discharge in structured personal interviews, preferably at the participant’s home. The place and time of the follow-up assessments are chosen for the highest possible convenience of the participants.

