### Data analysis

#### Statistical analysis

The statistical analyses will be calculated on an *intention-to-treat* basis to reduce the impact of dropouts during the follow-up. These will include all individuals with baseline values of the outcome variables. Missing follow-up values will be imputed. To check whether systematic dropouts during the baseline assessment influenced the results, we will run multivariable logistic regressions with dropout as a dichotomous outcome (yes or no). The study group, sociodemographic variables, and clinical parameters assessed during screening (such as MMSE and the 4A test) will be included as predictors. These analyses will be performed for (1) all dropouts, (2) dropouts due to death, and (3) dropouts due to withdrawal of informed consent. To describe the study sample, appropriate summary statistics such as the mean, median, minimum, and maximum for continuous variables and frequencies and percentages for categorical data will be used.

The primary analyses will use separate generalized linear models to test intervention efficacy. The main outcome variables at follow-up 1 (3 months after discharge) and follow-up 2 (12 months after discharge) will be the dependent variables. The model specification will correspond to the scale level of the outcome variable under investigation. B-ADL will be assessed with a linear mixed regression, while for readmissions into hospital and institutionalization, logistic models will be used. The models will be adjusted for age, sex, and living situation of the patients. The study group is the predictor of interest (CAU vs. intervention). To account for the stochastic dependency of patients treated in the different hospitals (Bielefeld and Greifswald), study center will be included as a random effect variable. The baseline value of the outcome variable will be included as a covariate to reduce residual variance and to account for inter-individual variance at baseline. A positive intervention effect is defined as a significant regression coefficient (one-sided test) of the study group variable. Missing data will be imputed by multiple imputations via chained equations, stratified by study group. The overall alpha of the different primary outcome analyses will be adjusted using the Bonferroni–Holm procedure [56].

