For the secondary analyses, sociodemographic variables (age under 80 or above 80), sex (man or woman), living situation (alone or not alone), and clinical parameters such as cognitive status, delirium, and frailty will be included. These variables either showed an impact in the DelpHi-MV study [24, 57] or are expected to moderate the health trajectory of elderly people in general. The inclusion of sociodemographic and clinical parameters should result in decreased residual variance and enhanced statistical power. To improve the quality of the regression models, possible interaction effects will be analyzed for study group, age group, living situation, and clinical parameters.

Economic evaluations will be conducted using methods that are consistent with those of published methodological guidelines for economic evaluations [58]. Health-care costs per patient will be calculated for a retrospective period of 3 months (follow-up 1) and 1 year (follow-up 2) from a public payers and societal perspective using published unit costs [59]. To analyze differences in quality-adjusted life years (QALYs) and costs, a linear mixed regression model will be used. The incremental cost-effectiveness ratio will be calculated using the incremental cost per QALY gained by the intervention compared with usual care. We will calculate the probability of the intervention being cost-effective at a wide range of willingness-to-pay margins using nonparametric bootstrapping to handle the sample uncertainty [60–62].

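### At the 3-month visit the readmission outcome rests on a 12-month look-back, nine months of which precede discharge and contain the index stay; no rule limits it to unplanned stays

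*Protocol article*

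**What the plan says.** The Outcomes section of the protocol article lists the endpoint: "Primary outcomes are ADL (which are a proxy for functionality after discharge), unscheduled readmissions, and premature institutionalization". The second main hypothesis, at the end of the Background, is that patients in the intervention arm "will have a lower frequency of unscheduled readmissions to hospital than PCI receiving CAU".

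One measure is given. Under Outcomes, "each participant will be asked how many times they have been hospitalized (unplanned and planned) within the last 12 months", and "This is one item in the Questionnaire on the Use of Medical and Non-Medical Services in Old Age (FIMA"). The same section says, in describing service utilization, that this questionnaire's scores show whether a service was used (1) or not (0).

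On timing, Study procedure states: "Follow-up assessments of all outcome measures for both groups will be conducted 3 months and 12 months after discharge". Statistical analysis states: "The main outcome variables at follow-up 1 (3 months after discharge) and follow-up 2 (12 months after discharge) will be the dependent variables", and on model type, "while for readmissions into hospital and institutionalization, logistic models will be used". Those models also adjust for the baseline value of the outcome.

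A shorter recall period appears only in the economic paragraph of Statistical analysis: "Health-care costs per patient will be calculated for a retrospective period of 3 months (follow-up 1"), with one year at follow-up 2.

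**The concern.** A readmission is an event after the index discharge. An item that looks back 12 months from a visit held 3 months after discharge mostly measures time before discharge. Those earlier stays cannot be affected by the intervention, and one of them is the admission through which the patient entered the trial. The item also asks about planned stays, whereas the endpoint and the hypothesis concern unscheduled ones.

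The 3-month analysis of one of three primary outcomes is therefore at stake. A comparison that is constant or heavily diluted would most likely be reported as no effect on readmission. It would also still take up a place in the Bonferroni–Holm procedure that the protocol applies across the primary outcomes.

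**Working it through.** **The plan's own figure.** The protocol gives no sample size or event rate for readmission. Its 199 per arm is based on activities of daily living with d = 0.25. It reproduces as a one-sided t-test at alpha 0.05 and 80% power (198.5, rounded up to 199), but says nothing about readmission.

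**Step 1: the window.** Months before discharge covered by the item = 12 − months since discharge.

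| Visit | Months after discharge | Months before discharge | Share before discharge |
|---|---|---|---|
| Follow-up 1 | 3 | 12 − 3 = 9 | 9/12 = 75% |
| Follow-up 2 | 12 | 12 − 12 = 0 | 0% |

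The index stay lies inside the nine months; it is not additional to them.

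**Step 2: index stay counted.** Every participant is enrolled as an inpatient, so a truthful answer at follow-up 1 is at least 1. If the binary outcome is any stay in the window, it equals 1 in both arms and the logistic model has no solution.

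**Step 3: index stay removed, earlier stays kept.** The protocol gives no admission rates, so these are assumptions: a constant rate r of 0.4 to 1.0 admissions per year and a true 30% reduction after discharge in the intervention arm. With expected count m, P(any) = 1 − exp(−m) for Poisson counts, or m/(1 + m) for negative binomial counts with dispersion 1.

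Example with r = 0.6, Poisson:
- Three-month window: control m = 0.6 × 0.25 = 0.15, P = 13.9%. Intervention m = 0.15 × 0.7 = 0.105, P = 10.0%. Odds ratio 0.68.
- Twelve-month look-back: control m = 0.6, P = 45.1%. Intervention m = 0.45 + 0.105 = 0.555, P = 42.6%. Odds ratio 0.90.

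Over the whole range and both distributions:

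| Outcome at follow-up 1 | Odds ratio |
|---|---|
| Unplanned stays since discharge (3 months) | about 0.67–0.70 |
| 12-month look-back without index stay, unadjusted | about 0.89–0.93 |
| Same, adjusted for any admission in the year before the index stay (simulated) | about 0.80–0.83 |

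The adjusted row is nearer to the planned model, because the covariate accounts for part of the earlier stays. It requires that indicator to be collected at baseline. The baseline list under Study procedure does not name the questionnaire that contains the item.

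**Step 4: power, as a second illustration.** Assume 25% versus 15% with a readmission within 3 months, and a probability q of another stay in the nine months before discharge, equal in both arms and independent of later stays. Each proportion becomes 1 − (1 − p)(1 − q). One-sided alpha 0.05, 199 per arm, unadjusted:

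| q | Control | Intervention | Difference | Power |
|---|---|---|---|---|
| 0 | 25.0% | 15.0% | 10 points | 80% |
| 0.2 | 40.0% | 32.0% | 8 points | 51% |
| 0.3 | 47.5% | 40.5% | 7 points | 41% |
| 0.5 | 62.5% | 57.5% | 5 points | 27% |

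**Step 5: planned stays.** The endpoint and the hypothesis say unscheduled, while the item covers both types. The text neither states that the types are recorded separately nor that only unplanned stays enter the analysis. This applies at both visits.

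**The case against.** The strongest reply is that the word readmission excludes the index stay by definition, that trained interviewers with access to patient records can identify it, and that the article gives no cut-point for turning the count into a binary outcome. This stands in part. The constant outcome in Step 2 is conditional on counting the index stay and is not the plan's stated analysis. A reader might infer that the 3-month model is certain to fail, but the documents do not support that. Removing the index stay, however, leaves the other pre-discharge stays in place.

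A second reply is that the 3-month costing period suggests a shorter recall at follow-up 1 and that a condensed article may simply omit it. That is plausible, but the costing text does not define the readmission outcome, and the Outcomes section states 12 months outright. The two need reconciling whichever was meant.

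Third, the unadjusted odds ratios overstate the dilution under a model that adjusts for baseline. This also stands, hence the adjusted row. If the admission rate after discharge is assumed to be double the earlier rate, the adjusted odds ratio is about 0.73–0.78, so the loss shrinks further but does not vanish.

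Fourth, mentioning both types of stay may mean only that they are recorded separately. That cannot be ruled out, so the fault is an unstated rule and not a settled decision to count planned stays. A reader might also infer that planned stays could reverse the effect; nothing in the documents supports that.

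Finally, a reader might extend the window problem to follow-up 2. There the look-back matches the post-discharge year, and only a visit held slightly early would reach back to the index stay.

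**Conclusion.** The point holds for follow-up 1. As written, the measure of a primary outcome covers nine pre-discharge months out of twelve, including the index stay, and no stated rule removes them. The outcome is either constant (index stay counted, any-stay definition) or diluted (index stay removed). Under the assumed rates and a true 30% reduction, an odds ratio of about 0.67–0.70 becomes about 0.89–0.93 unadjusted, or about 0.80–0.83 with a prior-year admission indicator as covariate. These sizes rest on assumed admission rates; the 75% share of the window rests only on the protocol. The missing restriction to unplanned stays affects both visits. It should be corrected before analysis, because a bare 12-month count does not show which stays came after discharge.

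**What to change.** Define the outcome as at least one unplanned admission after index discharge up to each visit, excluding the index stay. At follow-up 1 ask about stays *since you left hospital on [index discharge date]*; at follow-up 2 ask about stays since index discharge. Record the date and planned or unplanned status of every stay, and use only unplanned stays for the primary outcome. Reconcile the item in Outcomes with the time points and the 3-month costing period in Statistical analysis.

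For follow-up 1 interviews already held, reclassify stays from patient records where these are available, and report that stays at other hospitals may be missed. The article describes only a count, so admission dates cannot be assumed to exist in the interview data. Where records do not help, rely on the follow-up 2 window.

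The cost is a changed question stem in the tablet questionnaire, a small departure from the standard wording of the instrument, and some recoding. At the stated status 236 of 398 participants were enrolled and the last follow-up was expected on 30 November 2020, so at that point many interviews were still to come.

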**Fig. 2 Fig2:**
[figure not shown]
Schedule of enrollment, intervention, and assessments in accordance with the Standard Protocol Items: Recommendations for Interventional Trials (SPIRIT) guidelines. SCR screening at the time of admission to hospital, BL baseline after having provided written informed consent, *I*_1_ during hospital stay, *I*_2_ day of discharge, *I*_3_ up to 3 days after hospital discharge, *I*_4_ period up to 3 months after discharge, *FU*_1_ 3 months after discharge, *FU*_2_ 12 months after discharge

### Sample size

The estimated enrollment for the study is *n* = 398 participants plus their respective informal caregivers (where available). This sample size is necessary in the context of a complex intervention, which could not be proven to be efficacious in a smaller cohort. A sample size of *n* = 199 persons per arm is needed to detect effects on ADL with a Cohen’s *d* = 0.25 [47]. We expect Cohen’s *d* = 0.25 based on the DelpHi-MV study [24], which was approximately the size of the effect of the intervention on patients’ ADL (from preliminary analyses, since ADL were not the primary outcome in this trial, but a secondary outcome). As the Intersec-CM intervention is adapted from dementia care management, this should give a good estimate of what effect will be obtained. In a comparison between the intervention and control groups at a significance level of *p* = 0.05 and a statistical power of 80%, the sample size needed to obtain the same effect size as in the DelpHi-MV study (*d* = 0.25) is *n* = 199 patients per arm. This calculation includes that outcomes expected to deliver stronger effects are sufficiently powered.

Because of the longitudinal design, the sample size will decrease over time for various reasons. Loss to follow-up due to death, migration, withdrawal of informed consent, and nonparticipation for logistical and organizational reasons will occur. Migration is unlikely to have a large effect because the 70+ year-old group tends to be geographically stable. If a participant is lost to follow-up, efforts will be made to locate and recontact them. Data on those lost to follow-up will be included in the main analysis. Withdrawal of initial consent will be documented wherever possible together with the reasons provided. We expect that loss to follow-up will be approximately 30%, so that we expect at least *n* = 279 participants will provide a completed data assessment at the second follow-up visit.

In summary, the sample size is sufficient to detect even moderate effects on the outcomes. International studies are not readily comparable to the specificities of the German health-care system, and since this is the first randomized controlled trial addressing these research questions in Germany [48], we cannot precisely calculate our sample size based on previous studies and do rely to some extent on assumptions. The trial will aim to reach the sample size calculated and will be prolonged if recruitment takes longer than expected.

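### The 80% power for d = 0.25 assumes outcome data on all 398 participants and no Holm adjustment; at the 279 completers the plan expects at 12 months, an unadjusted B-ADL comparison has about 67%

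*Protocol article*

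**What the plan says.** The Sample size section sets the target: "The estimated enrollment for the study is *n* = 398 participants". It justifies this by stating that 199 "persons per arm is needed to detect effects on ADL with a Cohen" d of 0.25, a value taken from preliminary analyses of the DelpHi-MV study. At a 5% significance level and "a statistical power of 80%, the sample size needed to obtain the same effect size as in the DelpHi-MV study" is given as 199 per arm. The section does not say whether the 5% level is one-sided or two-sided, and it does not tie the power to a time point.

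The next paragraph of the same section turns to attrition: "We expect that loss to follow-up will be approximately 30" per cent. From this it expects at least 279 completed assessments at the second follow-up, 12 months after discharge. It says that those lost will still be part of the main analysis. The section closes: "In summary, the sample size is sufficient to detect even moderate effects on the outcomes".

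The Statistical analysis section supplies the rest. On sidedness: "A positive intervention effect is defined as a significant regression coefficient (one-sided test) of the study group variable". B-ADL is analysed by linear mixed regression with the baseline value as covariate, missing values are multiply imputed by study group, and the primary outcomes share an overall alpha through the Bonferroni–Holm procedure.

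**The concern.** Enrolment is exactly 2 × 199. The number said to be needed for 80% power is therefore the number randomised, and the section itself expects about three in ten of them to have no 12-month assessment. Either 199 per arm already contains a margin for loss, or the stated power is not the power at 12 months. The Holm procedure raises a second question, because the calculation uses the full 5% for one of three primary outcomes.

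B-ADL is the only outcome with a power calculation. If the 12-month result is not significant, readers will judge it against the stated 80% for d = 0.25. If the true figure is lower, such a result says less about an effect of that size than the article implies.

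**Working it through.** **Inputs.** d = 0.25, alpha 0.05, power 80%, 199 per arm, 398 enrolled, 30% loss and 279 completers come from Sample size. The one-sided test and the Holm adjustment come from Statistical analysis. The 1:1 allocation comes from Study procedure. The standard deviation is 1 because d is standardised.

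**1. Reproduce 199 per arm.** The normal approximation is n = 2(z₁₋α + z₀.₈)²/d².
- One-sided 5%: 2 × (1.645 + 0.842)²/0.25² = 198. The exact t-test gives 198.5, rounded up to 199.
- So 199 is the smallest complete-data sample size for a one-sided 5% t-test and holds no reserve for loss.

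**2. Completers.** 0.7 × 398 = 278.6, so 279, or 139.5 per arm.

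**3. Power for d = 0.25, one-sided 5%, unadjusted comparison.** Power = Φ(d√(n/2) − 1.645).
- n = 199: Φ(2.494 − 1.645) = 80.2% (t-test 80.1%).
- n = 139.5: Φ(2.088 − 1.645) = 67.1% (t-test 66.9%).

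**4. Effect detectable with 80% power at 139.5 per arm.** d = (1.645 + 0.842) × √(2/139.5) = 0.298, about 0.30.

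**5. First Holm step.** With three primary outcomes the first level is 0.05/3, one-sided, so z = 2.128.
- n = 199: Φ(2.494 − 2.128) = 64.3%.
- n = 139.5: Φ(2.088 − 2.128) = 48.4%.

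**6. Possible credit for baseline adjustment.** If d is on the unadjusted scale and the baseline correlates r with the 12-month value, the effective n is 139.5/(1 − r²). The article gives no r, so these values are assumptions.

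| Assumed r | Effective n per arm | Power, one-sided 0.05 | Power, one-sided 0.05/3 |
|---|---|---|---|
| 0.3 | 153 | 70.7% | 52.4% |
| 0.5 | 186 | 77.8% | 61.1% |
| 0.55 | 200 | 80.4% | 64.5% |
| 0.6 | 218 | 83.3% | 68.5% |

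A correlation of about 0.55 is needed to regain 80% before Holm.

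**7. Possible credit for imputation.** Assume, generously, that everyone missing at 12 months has a 3-month value correlating ρ with the 12-month value. The variance per arm is then proportional to (1 − ρ²)/139.5 + ρ²/199.
- ρ = 0.5: 0.00538 + 0.00126 = 0.00663, so effective n is about 151 and power about 70%.
- ρ = 0.7: 0.00366 + 0.00246 = 0.00612, so effective n is about 163 and power about 73%.

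Death and withdrawal of consent are among the listed causes of loss. Where they occur before 3 months there is no such value, so this is a favourable case.

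**The case against.** The strongest reply is that 67% describes an analysis the plan does not use. The planned B-ADL model adjusts for baseline and imputes missing values, and at a correlation of about 0.55 the baseline covariate alone would bring power back to 80% before Holm. That stands as a limit on the claim: 67% is the figure without covariate credit, and it should not be read as the trial's actual power. It does not rescue the stated 80%. The calculation gives no correlation and claims no credit, and it is unclear whether the d of 0.25 is already on an adjusted scale, in which case the credit would be smaller. Imputation can use what was observed but cannot supply outcomes that were not.

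Three stronger readings are tempting, and the article does not support them.

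- A reader might take the unqualified 5% as two-sided and call 199 simply too small. The Statistical analysis section specifies a one-sided test and 199 matches it. The only fault here is that the sample-size section leaves the sidedness unsaid.
- A reader might infer that the closing claim of sufficiency is false. It speaks of moderate effects and does not name d = 0.25. At 279 completers power is 80% for d of about 0.30, and for d = 0.5 it is Φ(4.176 − 1.645), about 99%. The sentence is vague and has not been shown to be wrong.
- A reader might infer that the article promises 80% power specifically at 12 months, or that the 3-month comparison falls equally short. The power statement names no time point and no 3-month loss is given, so the shortfall can be sized only for 12 months.

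It is also fair to say that 199 and 279 are each computed correctly, and that the article discloses the expected loss and its reliance on assumptions.

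**Conclusion.** The concern holds in this limited form. The 80% is right for a one-sided 5% test of d = 0.25 with all 398 participants observed and no Holm adjustment. On the article's own loss figure it does not carry over to 12 months: about 67% for an unadjusted comparison of 279 completers, a shortfall of about 13 percentage points, with 80% reached only at d of about 0.30.

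The first-step Holm figures, 64% with complete data and 48% with 279, take the family as the three primary outcomes. They apply when B-ADL is tested at the strictest level. If other primary outcomes have smaller p-values and are rejected first, the level for B-ADL rises toward 0.05 and the figures in step 3 become the ceiling for the unadjusted comparison.

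All figures assume equal loss in both arms and d on the unadjusted scale. Baseline adjustment may close part or all of the gap before Holm, depending on a correlation that the article does not state.

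**What to change.** Keep n = 398 and amend the Sample size section as follows.

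- State that alpha is one-sided 0.05.
- State that 80% power for d = 0.25 refers to 398 participants with outcome data, before multiplicity adjustment.
- Add the 12-month figures at the expected 279 completers for d = 0.25: about 67% before adjustment and about 48% at the first Holm step (one-sided 0.05/3), both without covariate credit.
- If credit for baseline adjustment is wanted, state the assumed correlation, its source, and the resulting power at both levels.
- Qualify the closing sentence by giving the effect detectable with 80% power at 279 completers: d of about 0.30 before multiplicity.

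The cost is a few sentences. Neither recruitment nor the analysis changes. The stated power becomes less favourable, and a non-significant 12-month result can then be read against the right figure.
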